### Study interventions

Eligible participants (Box 1) will receive a suite of interventions adapted from our previous work [14]. This will be in addition to current expected “standard” discharge care including a salbutamol weaning plan, medication prescriptions (when necessary), and hospital discharge letters as recommended in NSW Health guidelines [15]. The interventions include:

#### 1. Standardisation of asthma discharge

Participants discharged from the hospital will receive the “Asthma Resource Discharge package” which contains several pre-developed resources including an individualised asthma action plan (AAP) in colour [16], an asthma education booklet entitled “Asthma and Your Child–a resource pack for parents and carers” to improve parent’s/carer’s understanding of asthma that is available in multiple languages, a parent letter encouraging regular GP follow-up and uptake of annual influenza vaccination (as recommended in Global Initiative for Asthma (GINA) guidelines [17] and the Australian Immunization Handbook [18]), a letter for the child’s GP advising of their recent hospital presentation and discharge instructions including clinical best practice asthma tips, a letter for the child’s school/childcare including an individualised “Schools and Child Services Action Plan for Asthma Flare-up” [19] as approved by NSW Health and NSW Department of Education, an asthma leaflet with QR code link to access online based multimedia educational resources and access to monthly educational webinars facilitated by asthma clinical nurse consultants in the Aiming for Asthma Improvement in Children Initiative (AAIC, an NSW Health statewide asthma education organisation, www.asthmainchildren.org.au).

#### 2. Post-discharge care coordination

Parents/carers of the participating child will firstly receive a text message (SMS) reminder within 7 days of hospital discharge to remind them of regular GP follow-up and provide links to online resources and links to register for monthly educational webinars with the AAIC. In addition, local investigators will coordinate follow-up appointments with GPs and/or paediatricians through telephone or email to facilitate tele-consultation where possible and provide discharge instructions. Similarly, the child’s school or childcare service will be notified by email of the child’s recent asthma hospitalisation, provided an updated School & Child Services Action Plan [19] and reminded of the availability of online staff training resources including the AAIC eBook on Asthma First Aid in Children or training sessions for childcare staff via ACECQA (Australian Children’s Education & Care Quality Authority).

#### 3. Follow-up support for children with uncontrolled asthma

In addition to SMS messaging, children with uncontrolled asthma, as evidenced by an ACT/C-ACT score <19 on baseline questionnaire at enrolment, will be offered virtual home visits within 3 months of discharge from hospital to work through home environmental triggers, provide personalised asthma education and respond to parent’s concerns relating to their child’s asthma management plan. Assessment of environmental triggers including aeroallergens like house dust mite, pollens and grasses is important as they are key contributors to asthma disease and can result in frequent flare-ups [20]. Virtual home visits will be based on the “home environment checklist” (adapted from the home visit checklists of the Royal Brompton & Harefield Hospital and the United States Environmental Protection Agency) and performed by local clinical staff. These virtual home visits are a novel intervention within the three study LHDs. They will occur remotely using encrypted digital platforms and last for approximately 20–30 minutes.

For children identified as having severe asthma, defined by GINA as “asthma that is uncontrolled despite adherence with maximal optimized therapy and treatment of contributory factors, or that worsens when high dose treatment is decreased” [17], will also be offered joint telehealth consultation with a tertiary hospital-based paediatric respiratory consultant at the Sydney Children’s Hospital, Randwick and a locally based general paediatrician to develop a shared care plan. This is in keeping with National Asthma Council guidelines, which recommend that those on step 4 of asthma management algorithm be considered for specialist review [21].

### Aim 1: Impact assessment

#### Data collection

Changes in health service use for participating children will be evaluated by comparing the period of up to 5 years prior to their enrolment into the program (pre-intervention) and the period of up to 12 months following enrolment (post-intervention). This information will be gathered primarily from electronic care records at baseline (retrospectively gathering data on health service use in previous 5 years) and 12 months post-enrolment. Five years data pre-enrolment will be used to account for disruption from the COVID-19 pandemic.

As we are following up participants through time in each site, the pre- intervention time period of health service use for each participating site will serve as its own control for the post-intervention time period of health service use, that is, temporal control.

*Outcomes measures*. All outcome measures for the impact assessment will be assessed at baseline, 6 months, and 12 months post-intervention (Table 1). We will measure the changes over time (i.e., pre-intervention at baseline and post-intervention at 6-month and 12-month), and differences between intervention and temporal control groups on all indicators.

**Table 1 pone.0304711.t001:** Outcome measures of the impact assessment.

Outcome	Measure(s)	Source	Time point

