**Secondary outcome **			
Asthma related quality of life in children	miniPAQLQ	Online questionnaire	Enrolment, 6 and 12 months
Asthma control	ACT or C-ACT	Online questionnaire	Enrolment, 6 and 12 months
Medication adherence	BMQ	Online questionnaire	Enrolment, 6 and 12 months
Patient and family reported experiences *Parental satisfaction* *travel*, *costs*, *missed school/work*, *asthma-self management knowledge *	Purpose designed questionnaire	Online questionnaire	Enrolment, 6 and 12 months

*Demographics*. Key demographic data including age, gender, language spoken at home, country of birth, parent/carer level of education, Socio-Economic Indexes for Areas (SEIFA) data and indigenous status will be collected from electronic medical records and the baseline questionnaire.

*Healthcare utilisation*. Researchers will focus on 3 key areas of healthcare utilisation: i) GP visits, ii) ED visits, and iii) hospital admission. This will be collected from electronic records and questionnaires.

*Asthma control*. Level of asthma control will be assessed using the Asthma Control Test (ACT; for children ≥ 12 years old) or Childhood Asthma Control Test (C-ACT; children 5–11 years old). These validated tools consist of 5–7 Likert-type scale questions, with a 4-week recall, assessing the frequency of shortness of breath and general asthma symptoms, use of rescue medication, the effect of asthma on daily functioning, and overall self-assessment of asthma symptom control. The total score range is 0–27 (C-ACT) and 0–25 (ACT) respectively, with a score on either test less than 19 indicating uncontrolled asthma [22].

*Quality of life*. Quality of life of the child will be assessed by using the miniPAQLQ validated tool [23], which consists of 13 questions in three domains (activity limitation, symptoms, and emotional function). The activity limitation domain includes 3 questions relating to play, sports and other daily activities; symptoms domain has 6 questions on cough, wheezing and nocturnal awakening; emotional function domain contains 4 questions associated with items such as being frightened, frustrated or feeling different, being irritable or worried, etc. Scores for each item range from 1 (maximum impairment) to 7 (no impairment). Overall score will be calculated by dividing the total scores with 13.

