*Medication adherence*. Medication adherence will be assessed by using the Brief Medication Questionnaire (BMQ) [24] which consists of 12 screening questions of three domains (medication regimen, belief, and recall) with 1-week recall. The regimen domain has five items, with scores from 0 (adherence) to 1 (potential non-adherence). The belief domain has 2 items, with scores from 0 (no belief barrier) to 2 (belief barriers present). The recall domain has five items, with scores from 0 (no recall barriers) to >1 (recall barriers present). The questionnaire assesses patient adherence and barriers to adherence.

*Oral corticosteroid use*. Parents/Carers will be asked to recall retrospectively the number of days their child with asthma has required oral corticosteroids (e.g., prednisolone) in the preceding 6 months. Where possible, corroboration will be obtained on review of their electronic medical records if oral corticosteroids have been prescribed within a hospital setting.

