#### Data analysis

Interrupted time series (ITS) analysis will be used to assess the change in the time series patterns (intercept and slope) of health service use before and after intervention.

ACT score, asthma related quality of life, medication adherence, parent and child quality of life and family reported experiences will be compared at enrolment, 6 and 12 months after enrolment into the service. We will describe the outcomes at each time point using mean, standard deviation, median, and inter-quartile range. Since each participant will have three repeated measures over time, we will use multi-level regression analysis to examine the effect of the intervention on these outcomes, including in the models, a fixed effect for the intervention status (0 = pre-intervention, 1 = 6-month post-intervention, 2 = 12-month post-intervention) and calendar time of enrolment into the intervention for each participant, as well as a random effect of the Local Health District (LHD) to explore the degree of variation in the intervention effect by LHD. Our final model will exclude the random term in the presence of a statistically non-significant random effect. We will also consider participants are clustered within each LHD and use generalised estimating equations (GEE) approach in the regression analysis to account for the clustering.

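### The questionnaire outcomes have no temporal control, yet the plan promises one on all indicators and reads change since enrolment as the effect of the intervention

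*Protocol article*

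**What the plan says.** Under Aim 1, Data collection, the article defines its control. The sentence concerns the period before the intervention: the (pre-) "intervention time period of health service use for each participating site will serve as its own control". The historical data come from electronic records, described as "retrospectively gathering data on health service use in previous 5 years". The outcome-measures paragraph that follows promises two things: change over time from baseline to 6 and 12 months, and "differences between intervention and temporal control groups on all indicators".

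Table 1 gives every questionnaire outcome (miniPAQLQ, ACT or C-ACT, BMQ, family experience) the time points "Enrolment, 6 and 12 months". The ACT/C-ACT is described "with a 4-week recall"; the BMQ covers "three domains (medication regimen, belief, and recall) with 1-week recall". No recall period is stated for the miniPAQLQ.

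Under Aim 1, Data analysis, the interrupted time series is confined to health service use. For the questionnaires, "we will use multi-level regression analysis to examine the effect of the intervention on these outcomes". The fixed effects are status, coded 0, 1 and 2 for enrolment, 6 months and 12 months, and the calendar time at which each child enrolled. A random effect for health district is added.

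**The concern.** The promise covers all indicators, but the control covers only one family of them. The enrolment score cannot stand in as the temporal control, because the same sentence already lists change from baseline as a separate comparison.

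This matters because better asthma quality of life is part of the study hypothesis, and the child's quality of life is in the first research question. Children qualify through an emergency attendance or admission for asthma (Box 1). The discharge pack and the text message within 7 days tie the programme to that event. If the enrolment score is depressed by the attack, it will tend to rise afterwards whatever the programme does, and the model will label the rise an intervention effect. In addition, children scoring below 19 "on baseline questionnaire at enrolment" are offered virtual home visits. Regression to the mean in that subgroup would therefore coincide with an extra component of the programme.

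**Working it through.** **Structure of the questionnaire model**

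- Each questionnaire has one time point before the intervention and two after. One earlier point gives no prior trend and no change over a control period.
- Status 0/1/2 is the same variable as time since enrolment (0, 6, 12 months). Its coefficient is the mean change since enrolment from all causes.
- Calendar time of enrolment takes one value per child. It can adjust for when a child joined, but it cannot absorb change within that child.
- The district random effect and the clustering adjustment concern differences between districts and the standard errors. Neither supplies a comparison without the intervention.
- The interrupted time series does not include these outcomes, so its handling of trend and season does not reach them.

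**Sample size used**

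The article states 317 recruited, 15% attrition and 270 analysed. Check: 317 × 0.85 = 269.45, about 270; in reverse, 270/0.85 = 317.6, or 318. The step reproduces to within rounding.

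**Chance of a significant change when the programme does nothing**

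Inputs: n = 270 and two-sided 5% (both from the sample size section). A paired contrast of enrolment with one follow-up time is used as a simple stand-in for the model. *Assumptions, because the article gives no figures:* the attack lowers the enrolment score by 0.34 SD of the change score, and a share f of enrolment windows contains the attack.

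Mean shift: δ = f × 0.34. Rejection probability: P = Φ(δ√n − 1.960) + Φ(−δ√n − 1.960), with √270 = 16.43.

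| Share f | δ (SD of change) | δ√n | P |
|---|---|---|---|
| 10% | 0.034 | 0.56 | about 9% |
| 25% | 0.085 | 1.40 | about 29% |
| 50% | 0.170 | 2.79 | about 80% |
| 90% | 0.306 | 5.03 | about 99.9% |

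**The same question in score points**

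The SD of change is assumed to be 4, 5 or 6 points. The shift divided by (SD/√270) replaces δ√n.

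- Mean recovery of 0.5 point: 54%, 38%, 28%.
- Mean recovery of 1 point (for example, 25% of children recovering by 4 points): 98%, 91%, 78%.
- Mean recovery of 0.2 point (10% of children recovering by 2 points): 13%, 10%, 8%, counting significant improvement only.

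The result depends almost entirely on the share of affected windows and the size of the drop, and the article gives neither.

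**The case against.** Several points on the other side are sound.

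- **The outcomes are secondary.** The primary outcome, health service use, has a retrospective series of up to 5 years and its own time series analysis, and the sample size rests on emergency presentations. This stands and lowers the severity.
- **The limitation is disclosed.** The Discussion concedes that a one-group design limits comparison with usual care. It does so in general terms, names neither recovery nor regression to the mean, and leaves the promise and the effect wording in place. It is a partial answer.
- **The interval from attack to questionnaire is not fixed.** Box 1 looks back 12 months, so some enrolment windows will contain no attack. A reader might infer that most windows do, and hence that a false improvement is to be expected. The discharge-linked schedule makes overlap plausible, but the article does not establish how common it is.
- **The questionnaires differ.** A reader might extend the recovery argument to all of them. Only ACT/C-ACT has a stated window that clearly fits. The miniPAQLQ recall period is not given. The BMQ measures adherence and its barriers over one week, and an attack could even raise adherence for a time. Satisfaction and knowledge have no obvious recovery. The missing control applies to all four; the recall mechanism does not.
- **A covariate could seem to repair it.** One might add an indicator for an attack inside the enrolment window and read the intervention effect from the attack-free baseline. That would set an attack-free baseline against follow-up scores that may include attacks, so an inert programme would tend to look harmful. The model names no child-level term, so the contrast would also rest partly on differences between children. If 90% of windows held an attack, only about 27 of 270 children (10%) would anchor it.

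**Conclusion.** The contradiction is established by the text alone: the control comparison is promised on all indicators and exists only for health service use. It is equally firm that the questionnaire model, as specified, cannot distinguish an intervention effect from recovery or regression to the mean.

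The size of any false effect is not established. At the assumed 0.34 SD drop it runs from about 9% (10% of windows affected) through 29% (25%) to 80% (50%), against a nominal 5%. The documents support neither the claim that recovery will certainly be reported as benefit nor any extension of this point to the primary outcome. The point should be fixed, because it changes what the trial may conclude about asthma control and quality of life, but it concerns secondary outcomes and a limitation that is partly acknowledged.

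**What to change.** 1. Under Aim 1, Data collection, limit the temporal-control comparison to health service use.
2. Under Aim 1, Data analysis, describe the questionnaire results as uncontrolled change since enrolment instead of an intervention effect, and rest no causal claim about asthma control or quality of life on them.
3. Using the dates of asthma emergency attendances and admissions in the records already being extracted, report ACT/C-ACT change at 6 and 12 months separately for children with and without such an event in the 4 weeks before the enrolment score. Present this as a descriptive sensitivity display, not as an adjusted effect, since the two groups are different children.

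The cost is a change of wording, one derived variable and one extra table, with no new data collection. The price in substance is a weaker claim for the secondary outcomes.

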**Primary outcome **			
Health service use	• Hospital admissions • ED attendances • GP visits	Linked routinely collected medical records	Pre and post intervention

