## Hypotheses and aims

We hypothesise that a comprehensive virtually enabled asthma model of care that leverages digital technologies can provide continuity of care, improve asthma quality of life and lead to reduction in unscheduled hospital presentations in children with asthma aged 5–12 years living in rural NSW. We further hypothesise that our proposed model of care will reduce the cost of care devoted to this patient cohort and help to alleviate financial pressures facing families as a result of a child’s asthma diagnosis.

Asthma Care from Home aims to evaluate the impact (aim 1), implementation (aim 2) and cost effectiveness (aim 3) of a comprehensive virtually enabled asthma care initiative in three rurally based LHDs in NSW that a. supports families, communities and healthcare providers, b. is flexible and locally acceptable, and c. adopts innovations such as digital technologies so that asthma care can be provided ‘from home’ when necessary, thereby not only reducing the significant burden of potentially preventable asthma hospital presentations but also ensuring patients’, parents/carers and families satisfaction with healthcare delivery.

This project comprises of three related research questions:

What is the impact on asthma-related health system utilisation, child’s health related quality of life and parent/carer’s experiences?What is the cost effectiveness and cost impact for both the child’s family and the healthcare system by adopting this model?Can these results be used to support State-wide scale-up?

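### The primary outcome groups three unranked measures, including GP visits that the programme promotes, while the hypothesis concerns hospital presentations and only ED presentations are powered

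*Protocol article*

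**What the plan says.** All places are in the protocol article.

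- **Table 1, primary outcome.** Health service use, measured by "Hospital admissions • ED attendances • GP visits". The source is "Linked routinely collected medical records".
- **Aim 1, Healthcare utilisation paragraph.** The same three measures, again without order: "Researchers will focus on 3 key areas of healthcare utilisation: i) GP visits, ii) ED visits, and iii) hospital admission". On source it adds: "This will be collected from electronic records and questionnaires".
- **Hypotheses and aims.** The model is expected to "lead to reduction in unscheduled hospital presentations in children with asthma". No direction is given for GP visits.
- **Sample size calculation.** At least 317 children recruited and 270 analysed after 15% attrition, to detect a rate ratio of 2.6 in asthma-related ED presentations with 80% power at a two-sided 5% level. Admissions and GP visits do not appear.
- **Post-discharge care coordination.** A text message within 7 days is sent to "remind them of regular GP follow-up and provide links to online resources", and "local investigators will coordinate follow-up appointments with GPs and/or paediatricians through telephone or email". The discharge pack also holds a parent letter that encourages GP follow-up.
- **Aim 1, Data analysis.** An interrupted time series assesses intercept and slope of health service use. No component, direction or success rule is attached.

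**The concern.** Three parts of the same document point at three different targets. The hypothesis is about unscheduled hospital presentations, the power calculation is about asthma-related ED presentations, and the declared primary outcome also takes in admissions and GP visits.

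GP visits are the awkward member. The Background says that no system now secures GP follow-up after discharge, and the programme is built to supply one. If it works as designed, GP contact should go up while hospital contact goes down. A primary outcome that holds both, with no ranking and no direction, does not say which result would make the trial a success. That leaves room for selective emphasis once the results are known, in a one-group study that has no concurrent comparison to discipline the reading.

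**Working it through.** **1. The plan's own figures.** The attrition step holds: 270 / 0.85 = 317.6, and 317 × 0.85 = 269.5, so 317 and 270 agree within rounding. The power step cannot be reproduced because no baseline ED rate is given. Working backwards with a Wald test on the log rate ratio, and reading 2.6 as a fall (RR = 1/2.6):

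- implied baseline rate = (1.960 + 0.842)² × (1 + 1/RR) / (270 × (ln RR)²) = 7.85 × 3.6 / (270 × 0.913) ≈ 0.11 per child per period;
- a single-sample score test gives about 0.06, and a square-root transform about 0.05.

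The endpoint in the calculation is clear in every variant: asthma-related ED presentations only. The present point does not depend on the missing rate.

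**2. Targets side by side.**

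| Place | Target | Direction |
|---|---|---|
| Hypotheses and aims | Unscheduled hospital presentations | Fall |
| Sample size calculation | Asthma-related ED presentations | Ratio 2.6, two-sided test |
| Table 1 | Admissions, ED attendances, GP visits | None stated |
| Interventions | GP follow-up promoted by letter, SMS and appointments | Rise (inferred) |

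**3. If the three measures are tested separately**, each at 5%, with success on any one (an assumption, since the protocol states no rule):

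- under independence: 1 − 0.95³ = 0.143;
- upper bound without independence: 3 × 0.05 = 0.15.

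Controlling this by Bonferroni over three measures multiplies the required size by ((2.394 + 0.842) / (1.960 + 0.842))² = 1.334. That gives 270 × 1.334 = 360.1, so 361 analysed, and 361 / 0.85 = 424.7, so 425 recruited. Keeping 270 instead lowers power from 80% to Φ(1.960 + 0.842 − 2.394) = Φ(0.408) ≈ 66%.

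**4. If health service use were instead read as one total.** No summed composite is defined, so this is an illustration with assumed rates. Take 0.5 admissions, 1.5 ED visits and 4 GP visits per child-year before enrolment, a total of 6. Let both hospital measures fall by a factor of 2.6, so 2 / 2.6 = 0.77.

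- GP visits up 25%: (0.77 + 5) / 6 = 0.96 of baseline.
- GP visits up 50%: (0.77 + 6) / 6 = 1.13.
- GP visits doubled: (0.77 + 8) / 6 = 1.46.

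With 2 GP visits at baseline the ratios are 0.82, 0.94 and 1.19. A full success on hospital use could then look like little change, or a rise.

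**5. Source.** Table 1 gives linked records. The Healthcare utilisation paragraph gives records and questionnaires. The Aim 1 Data collection section says that the information comes mainly from electronic records, both for the period before enrolment and at 12 months. The three statements differ on whether questionnaires contribute to the primary counts.

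**The case against.** The strongest reply is that the measures are listed separately and Aim 1 promises results on every indicator. Fewer ED visits with more GP visits is exactly the pattern that the model seeks, and a reader can see it. The hypothesis and the sample size also show what the main target is. This stands: each measure is interpretable alone, and the trial does not lack a target. What remains is that Table 1 does not carry that target.

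Three stronger readings are tempting, and the documents do not support them.

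- *The primary outcome is a composite that cannot be interpreted.* No sum is defined anywhere. The ratios in step 4 apply only if someone forms one, and they rest on assumed rates.
- *There are six primary tests (intercept and slope for each measure), so the false-positive risk is about 26%.* The figure is 1 − 0.95⁶ = 0.265. The protocol does not say that six coefficients are each tested at 5% with success on any one. Independence is also implausible for level and slope from one series, or for ED visits and admissions in the same children. The handling of parameters may properly sit in an analysis plan that is not shown.
- *Questionnaire counts are added only after enrolment and bias the before/after ratio.* No section says so. Electronic records are the main source in both periods, there is a questionnaire at enrolment, and parents are asked elsewhere to recall the previous 6 months for steroid use. Only a difference in wording between sections is established.

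It may also be said that changing a published primary outcome in an open, single-arm study is more than an edit. That is fair and is counted as a cost below.

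**Conclusion.** The point holds as a misalignment within the protocol. The declared primary outcome is wider than the hypothesis and the powered endpoint, it ranks nothing, and it includes a measure that the programme is likely to push up. Success on the primary outcome as a whole is therefore undefined, although each measure can be read by itself.

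The size is a family-wise error of about 14%, at most 15%, on the assumption of three separate tests at 5% with success on any one. The expected rise in GP visits is inferred from the content of the intervention and is not stated by the protocol. Choosing the primary outcome belongs in the protocol, and Table 1 does fix it, so this is not a detail left to an analysis plan. It should be changed. The difference in source statements is a smaller matter to be settled at the same time.

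**What to change.** 1. In Table 1, name the asthma-related ED presentation rate as the single primary outcome, with a fall as the hypothesised direction. The test can stay two-sided.
2. State one primary parameter in advance, for example the 12-month rate ratio or the level change in the time series. Which one is the trial team's choice.
3. Make hospital admissions a secondary outcome. Make GP visits a process or secondary outcome, with an expected increase written down.
4. Reconcile Table 1, the Healthcare utilisation paragraph and the Data collection section, so that the primary count uses the same record source before and after enrolment. State what the questionnaire counts are used for.

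**Cost.** Admissions and GP visits lose primary status. The change to a published primary outcome must be recorded as a dated amendment with its reason, preferably before post-enrolment utilisation data are examined. The stated 317 recruited, 270 analysed and two-sided 5% stay as they are, because the calculation already uses this endpoint. Keeping all three as primaries under a Bonferroni correction would instead need about 361 analysed and 425 recruited, or accept about 66% power.
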